## Abstract

**Aim:**

Social determinants (SD) such as age, gender, ethnicity, postal code, or socioeconomic status, as well as health beliefs strongly impact health outcomes. This study aims to analyze the influence of SD on adherence to healthy lifestyle recommendations among individuals with prediabetes.

**Design:**

This sequential explanatory mixed-methods study will include an initial cross-sectional analysis of quantitative data, followed by a qualitative ethnomethodological study using critical discourse analysis.

**Methods:**

The quantitative analysis will use data from 103 participants with prediabetes included in the intervention arm of the PREDIPHONE trial. The relationship between adherence to the lifestyle modification intervention (diet and physical activity) and sociodemographic characteristics will be explored by multivariable linear regression. The qualitative study will explore how gender, social class, and other factors (such as social and family support, knowledge about one’s health condition, health beliefs, and patient-professional relationship) can influence adherence to lifestyle changes in a selected subgroup of individuals. Data generation techniques will include semi-structured interviews, discussion groups, support network mapping, and the researcher’s field diary. The rigor strategies that will be applied include triangulation, data saturation, and reflexivity.

**Discussion:**

Prediabetes exhibits an uneven distribution, disproportionately affecting individuals from underprivileged social classes, directly impacting on adherence behaviors. Our study can guide the development of health interventions tailored to individuals with prediabetes, focusing on addressing social disparities in lifestyle modification.

**Patient or public contribution:**

Participants will contribute through semi-structured interviews and discussion groups, providing insights into their experiences on adherence to lifestyle changes.

**Clinical trial registration:**

ClinicalTrials.gov, identifier NCT06488677.

## Background

Type 2 diabetes (T2D) is a major risk factor for adult morbidity and mortality and represents a public health burden due to its rising global prevalence (1). According to a recent systematic review, 529 million people worldwide suffered from T2D in 2021. This number is estimated to grow to a prevalence of 1.31 billion by 2050 (2). T2D is preceded by prediabetes, a phase characterized by higher-than-normal blood glucose levels that do not reach the threshold required for a T2D diagnosis (3). Currently, approximately 7.5% of the adult population is affected by prediabetes, and by 2030, more than 622 million people worldwide are projected to have this condition. It is estimated that 70% of people with prediabetes will eventually develop T2D, with a mean annual incidence rate ranging from 5 to 10% (4). Notably, the risk of developing T2D extends beyond physiological factors. Social determinants (SD) such as age, gender, ethnicity, postal code, or socioeconomic status, and health beliefs are strong predictors of disease onset and progression (1). Populations with a low socioeconomic status (i.e., economically disadvantaged backgrounds, lower health literacy levels, lower educational status, and often, from ethnic and racial minorities), are known to experience reduced access to healthcare including health promotion programs (5). They also have lower adoption rates of health behaviors, such as physical activity (PA) and healthy diet, which increases their risk of chronic diseases such as T2D and their likelihood to suffer inequalities in mortality (6).

Despite strong evidence that lifestyle interventions prevent T2D, individual adherence varies widely (7). To date, the majority of interventions targeting adherence have been limited to the pharmacological sphere and have often overlooked the complexity of the phenomenon. In the context of chronic diseases, it is essential to integrate social and contextual factors to develop personalized strategies to improve adherence and sustain healthy behaviors (8).

Since SD strongly influence adherence to healthy lifestyle changes, deficiencies in any of the SD can create significant barriers to self-care for individuals with T2D (9). Studies exploring factors that can potentially influence the adherence process cover individual aspects such as age, gender, health beliefs, the patient-professional relationship, and social factors such as socioeconomic status, support networks, social cohesion, and family support (10).

Age has been shown to be a determining factor on adherence to healthy lifestyles as older individuals demonstrate better adherence in the management of T2D than younger ones (11). Gender differences also influence self-care, with women showing higher adherence rates despite having less time available for PA compared to men (12). Health beliefs are also a vital element that can modulate self-care behaviors. In the case of prediabetes, the perception of the risk of progressing to T2D is generally low, which could limit adherence to positive lifestyle changes (13). The patient-professional relationship, including health communication, is another aspect associated with disease management. A lack of personal touch in communication can lead to superficial and distant interaction, which can negatively affect treatment adherence (14). Moreover, individuals with a high socioeconomic status adopt and maintain healthier behaviors more frequently than those with a low socioeconomic status (15). Social support and cohesion also emerge as relevant adherence behaviors. Support network has been associated with adherence behaviors and health promotion, while the lack of it has a negative effect on adherence (2). Finally, family support can significantly influence self-management, as patients with more family support have higher levels of self-care and compliance to pharmacological treatment (16).

Successful adherence to lifestyle modifications involves more than individual effort and responsibility; it requires understanding the interplay between sociodemographic variables and the psychosocial environment within the individual’s broader context (13).

For all of the above, this study aims to explore the influence of SD on adherence behaviors in individuals with prediabetes included in the PREDIPHONE trial, using a mixed-methods sequential explanatory design. The findings from both the quantitative and qualitative phases will be integrated to offer a comprehensive understanding of the complex phenomenon of adherence.

## Methods/design

### Purpose of the study

The main aim of this study is to analyze the influence of SD on adherence to healthy lifestyle recommendations in individuals with prediabetes included in the intervention arm of the PREDIPHONE trial. The project hypothesizes that social determinants of health (gender, age, education level, and socioeconomic status) influence the level of adherence to a healthy lifestyle intervention in these individuals. Additionally, the following secondary hypothesis are proposed:

1) Positive psychosocial factors, social environment, and patient-professional relationship may increase adherence to a healthy lifestyle intervention in people with prediabetes.2) Individuals from socioeconomically disadvantaged backgrounds are likely to exhibit lower adherence to the intervention.

The study aims to achieve the following objectives:

(1) Evaluate whether SD, specifically gender, age, social class, and educational level, influence adherence to healthy lifestyle recommendations—including a healthy diet and regular PA—among individuals with prediabetes.(2) Explore how perceived contextual and social factors—such as social and family support, knowledge about one’s health condition, health beliefs, and the patient-professional relationship—can act as facilitators or barriers to adherence to lifestyle changes in these individuals.

To guide the integration of the quantitative and qualitative findings, the following mixed-methods research question is proposed: *How will the relationship between sociodemographic variables—namely age, sex, educational level and socioeconomic status—and levels of adherence to a lifestyle modification intervention help explain contextual and interpersonal factors contributing to adherence to healthy lifestyle recommendations among individuals with prediabetes?*

### Design

This mixed-methods study is conducted with a sequential explanatory design, integrating quantitative analysis with an ethno-methodological qualitative study. The first phase involves a quantitative cross-sectional analysis of data from the PREDIPHONE trial. The results of this quantitative phase will inform the subsequent qualitative phase. The qualitative phase will employ an ethnomethodological framework along with a critical discourse analysis (CDA) approach. Ethnomethodology, as an interpretative sociological perspective, focuses on understanding how individuals attribute meaning to their social interactions and daily practices (17). On the other hand, CDA serves as a methodological tool that critically examines speech, text, and language to uncover the sociocultural and political realities of specific social contexts underlying discourse constructs. These approaches will be used in a complementary way: ethnomethodology will guide the interpretation of experiences and meanings constructed in everyday interactions, while CDA will examine how these meanings are shaped by broader social, cultural, and power structures, also serving as a tool for social critique and transformation (18). Finally, methodological integration will involve connecting participants across phases, building on quantitative findings, and weaving together qualitative and quantitative results to identify convergences and divergences.

The adoption of this design can facilitate a deeper understanding of the complexity surrounding adherence behaviors. The two phases of this study are outlined in Figure 1.

**Figure 1 fig1:**
[figure not shown]
Study flow-diagram.

### Quantitative phase (Phase 1)

The quantitative phase will consist of a cross-sectional analysis of data from the intervention arm of the PREDIPHONE trial (19). Data from 103 participants randomized to the intervention arm will be used to analyze the relationship between sociodemographic variables and adherence to the lifestyle intervention (diet and PA). Baseline data will be used to describe the sample.

#### The PREDIPHONE trial

The study design and methods of the PREDIPHONE trial have been previously described (19). Briefly, the PREDIPHONE trial is a randomized controlled trial aimed at evaluating the effectiveness of a nurse-led personalized telephone lifestyle intervention in reducing fasting plasma glucose (FPG) in adults with prediabetes, compared to automated text messages (SMSs). Between May 2021 and September 2022, a total of 206 participants were screened and recruited in 5 primary care centers of Palma, Mallorca.

Eligibility criteria included: age between 20 and 75 years, FPG between 100 y 125 mg/dL; body mass index (BMI) between ≥27 and <40 kg/m^2^; and written informed consent. Further details of the inclusion/exclusion criteria can be found in the published protocol.

Randomization was performed using permuted blocks of 4 in a 1:1 ratio via an internet-based program (OxMaR). The allocation was concealed to all staff members involved in the trial.

Participants allocated to the intervention group received personalized dietary and PA advice throughout the 9-month intervention period. At baseline, participants received supporting information material and agreed upon behavioral goals and action plans with the nurse. Nurses delivered between 8 and 12 individual telephone consultations to provide dietary and PA advice and assess compliance to recommendations. The consultations were structured according to the 5A’s behavior change model (Assess, Advise, Agree, Assist, Arrange), encouraging participants engagement in self-management. Goals and action plans were individualized based on baseline behavior and preferences.

Dietary advice followed a four-step approach: promoting Mediterranean dietary choices, using the Healthy Eating Plate model, educating on portion sizes, and, when appropriate, advising on caloric restriction. Participants were also encouraged to reduce salt, stay hydrated, and read food labels. Physical activity advice followed the 2020 World Health Organization (WHO) guidelines, recommending 150–300 min of moderate or 75–150 min of vigorous aerobic activity per week, along with strength training and reduced sedentary time. A five-step model was used to gradually increase frequency from one to three days per week of both exercise types. Participants were also encouraged to include stretching after each session.

Participants in the control group received a total of 150 automated SMSs (160 characters) on lifestyle advice throughout the 9-month intervention period.

Study data were collected at baseline, at months 4 and 9 of the intervention period, and at month 15 (post-intervention).

### Qualitative phase (Phase 2)

#### Theoretical framework

This study will be conducted within the critical-social paradigm, focusing on how SD (specifically gender and social class) can influence health behaviors and, in turn, generate health inequalities or inequities. The critical-social paradigm emerged as a tool to understand societal conditions as a basis for social transformation. In terms of health, by considering more deeply the sociocultural context of the individuals, nurses can work to empower them to adopt a critical perspective on their health, contributing to reduce health inequalities or inequities (20).

The WHO’s Conceptual Framework for Action on the Social Determinants of Health will be used to understand and describe the relationship between SD and health (21). Specifically, the influence of social class on adherence will be explored using the perspectives of Marx, Weber, and Wright (22). Social class is a fundamental factor that influences how relationships and processes develop, thereby creating and perpetuating significant inequalities in society. These deeply rooted inequalities are important to consider when analyzing why individuals adhere or do not adhere to healthy behaviors. Essentially, social class affects various aspects of life, including access to resources and health opportunities, which can impact one’s ability to maintain healthy habits.

The influence of gender on adherence behaviors will be addressed through two theories: Nancy Fraser’s three-dimensional theory and Carme Valls’ middle-range theory on gender and health. Nancy Fraser’s perspective will contribute to exploring how gender-related injustices are reflected in the health domain (23). Carme Valls’ theory can contribute to understand how gender inequalities intersect with other forms of oppression, such as social class and race, impacting a variety of health phenomena (24).

The patient-professional relationship will be analyzed using Jürgen Habermas’ Theory of Communicative Action (TCA) (25) and Paulo Freire’s Learning Theory, or more specifically, his concept of Popular Health Education (26). These theories can be applied to the health domain to help understand how the patient-professional communication can assist in improving self-care practices.

In the health context, TCA can help examining how nursing communication can empower and influence health behaviors both rationally and humanely. Communication in health should strengthen trust, lead to autonomy, and provide support throughout the process, respecting the patients’ rights to speak and be heard (27). The Paulo Freire’s Learning Theory and his concept of Popular Health Education can be applied to explore the role of nurses in acknowledging and respecting individual knowledge to eventually transform reality through autonomy and fostering the development of critical individuals who are aware of their own needs (26).

## Participants

### Quantitative phase

The quantitative phase will include 103 participants of the PREDIPHONE trial assigned to the intervention group who completed the 9-month intervention period. Participants from the control group or those who withdrew from the trial will be excluded. With a sample of 103 subjects, there is a statistical power greater than 90% to detect correlations ranging from 0.4 to 0.7, assuming a significance level below 0.05.

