## Data collection and analysis

### Quantitative phase

Adherence to the intervention will be measured through the generation of a composite index divided into quartiles. Participants scoring below the 25th quartile will be classified as “low adherent,” while those scoring above the 75th will be classified as “high adherent.”

Dietary adherence will be assessed using the 14-item PREDIMED Mediterranean Diet questionnaire (29); PA adherence will be evaluated using the REGICOR Abbreviated Questionnaire on PA in leisure time (30). The results from the dietary and PA questionnaires will be standardized and converted into z-scores to achieve a standard deviation of 1 and a mean of 0. These scores will be combined into a single value, which will be divided into quartiles of adherence.

Sociodemographic data (age, gender, educational level, and social class) will be collected during the baseline visit, in accordance with the study protocol. According to the occupation declared, subjects will be categorized as white or blue collar (22).

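### The adherence index measures diet and activity levels, so a social gradient that exists regardless of the nurse calls can be reported as a gradient in adherence to them

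*Protocol article*

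**What the plan says.** Under Purpose of the study, the main aim reads: "analyze the influence of SD on adherence to healthy lifestyle recommendations in individuals with prediabetes included in the intervention arm of the PREDIPHONE trial". Of the two secondary hypotheses in that section, the second is worded more narrowly: "Individuals from socioeconomically disadvantaged backgrounds are likely to exhibit lower adherence to the intervention".

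Under Data collection and analysis, Quantitative phase, the outcome is named and built: "Adherence to the intervention will be measured through the generation of a composite index divided into quartiles". Its ingredients are the 14-item Mediterranean diet questionnaire and the abbreviated leisure-time activity questionnaire: "The results from the dietary and PA questionnaires will be standardized and converted into z-scores". As described, the index holds no change from baseline, no count of calls taken and no measure of goals met. The Phase 1 description says of baseline: "Baseline data will be used to describe the sample". The regression adjusts for potential confounders that are not named.

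The Participants section defines the analysis set for this phase as follows: "The quantitative phase will include 103 participants of the PREDIPHONE trial assigned to the intervention group who completed the 9-month intervention period". Its next sentence sets the exclusions: "Participants from the control group or those who withdrew from the trial will be excluded". The comparator is described under The PREDIPHONE trial: "Participants in the control group received a total of 150 automated SMSs (160 characters) on lifestyle advice throughout the 9-month intervention period". That section gives 206 people recruited with 1:1 allocation, and data collection at baseline and months 4, 9 and 15.

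**The concern.** An index of what people eat and how active they are can be computed for anyone, including someone who never received a nurse call. It becomes a measure of adherence to a programme only if something ties it to that programme: change since the programme began, uptake of its contacts, attainment of its goals, or a comparison with people who did not get it. The article describes none of these.

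The Background itself states that people of high socioeconomic status take up and keep healthier behaviours more often, so the authors expect a gradient that owes nothing to the telephone calls. If the index shows lower values in blue-collar participants, two readings remain open. They may have followed the nurse programme less. Or their diet and activity scores may be lower whatever they receive, and may have been so at baseline. The planned analysis gives the same result under both, and the label on the outcome points to the first. The readings also matter for the stated use of the study, guidance for tailored programmes: a general lifestyle gradient and a weaker response to nurse calls suggest different things to tailor.

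**Working it through.** **Inputs from the article.** n = 103 in the intervention arm; 206 recruited at 1:1, so 206 − 103 = 103 in the SMS arm; significance level 0.05 (sidedness not stated, two-sided assumed); stated power above 90% for correlations of 0.4 to 0.7.

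**Assumed inputs.** Background correlation r between a social determinant and the index of 0.2, 0.3 or 0.4. For the simulation: a 50/50 class split, a baseline to follow-up correlation of 0.6, and no gradient specific to the nurse calls.

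**1. The plan's own figure.** Power = Φ(atanh(r)·√(n−3) − 1.96), with √(103−3) = 10.
- r = 0.4: Φ(4.236 − 1.96) = Φ(2.28) = 98.9%.
- r = 0.7: Φ(8.673 − 1.96), about 100%.

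The stated power is correct and this point does not change it.

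**2. How often a background gradient alone is significant in the planned analysis.** Same formula:
- r = 0.2: Φ(2.027 − 1.96) = 53%.
- r = 0.3: Φ(3.095 − 1.96) = 87%.
- r = 0.4: 99%, as in step 1.

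**3. What baseline scores inside the intervention arm can do.** Share of simulated trials with p < 0.05 when the gradient was fully present at baseline and did not change:

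| Analysis | r = 0.2 | r = 0.3 | r = 0.4 |
|---|---|---|---|
| Level of the index, intervention arm | 52% | 88% | 99% |
| Level with baseline as covariate, intervention arm | about 18% | about 32% | about 51% |
| Change from baseline, intervention arm | about 5% | about 5% | about 5% |
| Determinant-by-arm term, both arms | about 5% | about 5% | about 5% |

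Change from baseline removes a fixed gradient without the control arm. Covariate adjustment removes only part of it, because one baseline reading does not carry the whole class difference.

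Now let class shift behaviour after baseline equally in both arms, by an assumed 0.3 or 0.5 SD. Change within the intervention arm is then significant in about 39% or 78% of runs, while the determinant-by-arm term stays near 5%. A concurrent arm covers that case; baseline data alone do not.

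**4. How precise the between-arm comparison would be.** The SE of a difference of two Fisher z values is √(1/100 + 1/100) = 0.141.
- 95% half-width: 1.96 × 0.141 = 0.28.
- Difference detectable with 80% power: (1.96 + 0.84) × 0.141 = 0.40.
- Power for a gradient present in one arm only, Φ(atanh(r)/0.141 − 1.96): 30% at r = 0.2, 59% at r = 0.3, 85% at r = 0.4.

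The comparison can serve as a benchmark but is too imprecise to decide how the conclusion is worded.

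**The case against.** The strongest reply is that restriction to the intervention arm is deliberate and consistent. The main aim, the Phase 1 description and the participant criteria all say so, and no nurse-versus-SMS contrast is claimed. Phase 1 also selects people for interviews and groups that ask about the relationship with the professionals. This stands. A reader might infer that leaving out the SMS arm is itself the error, and the article does not support that. The source of the ambiguity is a level-based index under a label that promises more, and step 3 shows that part of it can be removed without the SMS arm.

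Second, most of the article speaks of adherence to lifestyle recommendations, and under that name a level of diet and activity is a reasonable outcome. This is largely right and makes the correction small. But the Phase 1 description, the qualitative sampling criteria, the definition of the index and a secondary hypothesis all speak of adherence to the intervention.

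Third, the unnamed confounders might include baseline scores. They might, so mislabelling is possible and not certain. The only use of baseline that the article states is description, and adjustment would deal with the problem only in part.

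Fourth, the SMS arm was itself given lifestyle advice. Equal gradients in the two arms are compatible with a real adherence gradient in both. A rule that reserves the term adherence to the nurse programme for determinants whose gradients differ between arms would therefore be unsound. With the power in step 4 it would also often relabel a true nurse-specific gradient as general.

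Fifth, the article reports visits for the trial as a whole and does not state that both questionnaires were given in both arms. That is likely but needs confirming.

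**Conclusion.** The point holds for the outcome and its label. The index measures levels of diet and activity, so the planned regression can establish a social gradient in lifestyle among people who were given advice. It cannot establish that disadvantaged participants adhere less to the nurse intervention, which is what the secondary hypothesis asserts.

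The size depends on a background gradient that the article does not quantify. For r between 0.2 and 0.4 the planned test is significant with probability 53% to 99% even if nothing is specific to the calls. A reader might take those figures as a false-positive rate. They are not one: the association in the intervention arm would be real, and only its interpretation would be at fault. A reader might also infer that the study is meant to redesign the nurse programme. The Abstract and Discussion speak of tailored health programmes in general, so the claim is only that the two readings suggest different tailoring.

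The precision figures assume about 103 analysable people per arm and simple correlations. Fewer completers would widen the interval.

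**What to change.** 1. Keep the intervention-arm regression as primary, in line with the declared aim. Name its outcome consistently as level of diet and activity, or adherence to lifestyle recommendations, and report its result as a social gradient in those behaviours and not as response to the nurse calls. Reword the secondary hypothesis, or state that this analysis does not test it in its narrow sense.

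2. Add one planned secondary analysis. Compute the same index in the SMS arm, standardised on both arms together, and score baseline with the same means and SDs. Use each participant's baseline score; change from baseline gives the clearer by-arm coefficients (step 3). Fit the same determinants with determinant-by-arm terms. Report each coefficient by arm and the difference with its 95% CI, as a descriptive benchmark.

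3. State in advance that the wording of conclusions does not depend on the significance of the difference, because the comparator is active and the estimate imprecise.

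4. Limit the control-group exclusion to the primary quantitative model and the qualitative phase, where it is appropriate.

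The cost is one further analysis of data the parent trial should already hold, once it is confirmed that both questionnaires were collected in the SMS arm, plus some edits to wording. No participants are added, and neither the primary model nor the Phase 2 sampling changes. The price is more cautious conclusions.
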